#### Predictive Models Using Resting State EEG

To predict drowsiness-mediated behavioral performance, the proposed model leverages resting-state EEG recordings obtained prior to task execution. The primary behavioral end point is SDLP, which is dichotomized into 2 classes: “Good Performance” and “Poor Performance” based on the 33rd and 66th percentiles of the SDLP distribution. This percentile-based approach ensures approximately balanced class sizes, and the resulting thresholds and participant categorizations were validated by domain experts.

Considering the nonstationary nature of EEG signals and their susceptibility to interindividual variability, machine learning methods capable of handling such variability will be prioritized. Feature extraction and selection will be guided by SHAP (Shapley Additive Explanations) values computed on the training set. Channels and features with high importance will be selected and then evaluated on a separate validation subset within each fold. Performance will be reported on a completely unseen test set to prevent leakage.

A leave-one-subject-out cross-validation strategy will be applied to provide a robust evaluation under intersubject variability. Within each fold, to optimize hyperparameters and feature selection, a nested validation set will be defined by randomly selecting a subset of participants from the training pool (ensuring no overlap with the test participant). All preprocessing, feature selection, and hyperparameter tuning will be performed exclusively on the training and validation subsets, with the test participant held out to avoid information leakage.

Classification will be performed using CatBoost, an ensemble-based gradient boosting algorithm suitable for tabular and heterogeneous data. To enhance generalizability and benchmark the findings across distinct algorithmic frameworks, additional classifiers, including radial basis function support vector machine, decision trees, logistic regression, and extreme gradient boosting, will also be applied. Demographic and behavioral covariates (eg, age, gender, chronotype, daydreaming frequency, and sleep history) will be optionally included to account for residual interindividual variability.

Model performance will be evaluated using accuracy, precision, recall, and *F*_1_-score, reporting both macroaveraged and weighted-averaged metrics to account for potential class imbalance. Comparing these metrics allows assessment of classifier sensitivity to imbalanced classes. Bootstrapping and permutation testing will be applied to evaluate the statistical significance and robustness of the results, ensuring that predictive performance is not due to chance.

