### Participants

#### Sample Size Calculation

This study is exploratory, since, to our knowledge, no other study has used the OSS to predict manifest sleepiness. Thus, because no data would allow us to statistically determine the number of participants required, this number has been arbitrarily set to 40 healthy volunteers. We believe this number will facilitate preliminary exploration at both inter- and intraindividual levels with an appropriate protocol.

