### Resting-State EEG Predictive Advantage

Unlike conventional automatic drowsiness detection systems that identify spontaneous drowsiness or related performance declines in real-time —often too late to prevent impairments or accidents— our approach might predict drowsiness-induced performance deterioration in advance, enabling timely intervention with effective countermeasures to prevent functional decline. The aim is to assess the cognitive readiness and forecast the likelihood of either good or impaired performance before the task.

Like certain algorithms, we will leverage machine learning analyses while integrating interindividual characteristics, such as age, sex, chronotype, and accumulated sleep deprivation. This personalized approach aims to enhance predictive accuracy.

By leveraging automatic sleep pressure quantification through resting-state EEG data—adjusted for interindividual characteristics— our study will provide valuable insights into individuals’ vulnerability to drowsiness before critical lapses in attention or vigilance occur. This predictive capability enables proactive interventions, such as fatigue management strategies, to prevent performance deterioration and reduce the risk of accidents.

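### Two SDLP cut-points with two balanced classes imply that the middle third is left out, so accuracy on the outer thirds would overstate performance for an unselected driver

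*Protocol article*

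**What the plan says.** The section Predictive Models Using Resting State EEG defines the outcome of the prediction model: "The primary behavioral end point is SDLP, which is dichotomized into 2 classes". The classes are Good and Poor Performance, and they are formed "based on the 33rd and 66th percentiles of the SDLP distribution". The next sentence describes the result: "This percentile-based approach ensures approximately balanced class sizes, and the resulting thresholds and participant categorizations were validated by domain experts".

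Validation is by participant: "A leave-one-subject-out cross-validation strategy will be applied to provide a robust evaluation under intersubject variability". The safeguard against leakage reads "All preprocessing, feature selection, and hyperparameter tuning will be performed exclusively on the training and validation subsets". The performance measures are given next: "Model performance will be evaluated using accuracy, precision, recall, and" F1-score, with macroaveraged and weighted versions, followed by bootstrapping and permutation testing.

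The Discussion, under Resting-State EEG Predictive Advantage, gives the purpose: to "forecast the likelihood of either good or impaired performance before the task".

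The article does not say what happens to SDLP values between the two percentiles, either in training or in testing.

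**The concern.** A single cut-point makes two classes, and two cut-points make three groups. The article names two cut-points but only two classes, and calls those classes approximately balanced. The natural reading is that the lowest third is Good, the highest third is Poor, and the middle third has no label.

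If the middle third is also missing when the held-out participant is scored, the test set has been selected on the outcome being predicted. The values removed lie nearest the good/poor boundary, where classification is hardest. Leave-one-subject-out validation, nested tuning and bootstrapping do not correct this, because all of them would run on the same selected values.

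At stake is the size of the performance claim for the second main objective. An operator assessed before a task has no SDLP value yet, so nobody can set the case aside because the drive will prove intermediate. Performance on the outer thirds answers an easier question than the one the Discussion asks.

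**Working it through.** The article states no accuracy figure or power calculation to reproduce. Under Sample Size Calculation it says that "this number has been arbitrarily set to 40 healthy volunteers". The one stated property that can be checked is class balance.

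**Step 1: number of drives.** Each test block contains one driving simulation (Experimental Session 1). There are 3 blocks in session 1, and 6 + 3 in session 2 (Experimental Session 2). Planned drives: 40 × (3 + 6 + 3) = 480, assuming none is missing.

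**Step 2: which reading gives balanced classes.**
- At or below the 33rd percentile: 0.33 × 480 ≈ 158
- Between the cut-points: 0.33 × 480 ≈ 158
- Above the 66th percentile: 0.34 × 480 ≈ 163

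| Handling of the middle group | Good : Poor | Balanced? |
|---|---|---|
| Left out | 158 : 163, or 49 : 51 | yes |
| Merged into Poor | 33 : 67 | no |
| Merged into Good | 66 : 34 | no |

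Only leaving the middle out agrees with the balance statement. If the labelled unit is the participant, the middle group is 0.33 × 40 ≈ 13 of 40.

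**Step 3: effect on accuracy.** The documents give no correlation between the EEG score and SDLP, so a range is assumed. Let the score S and SDLP Y be standard bivariate normal with correlation r, and predict Poor when S > 0.
- All drives, Y split at its median: accuracy = 2 × Φ₂(0, 0; r) = 1/2 + arcsin(r)/π.
- Outer groups only, with z₁ and z₂ the normal 33rd and 66th percentiles: accuracy = [Φ₂(0, z₁; r) + 1 − Φ(0) − Φ(z₂) + Φ₂(0, z₂; r)] / (0.33 + 0.34).

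Example at r = 0.5, all drives: 1/2 + 0.5236/3.1416 = 0.667.

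| Assumed r | Outer groups only | All drives, median split | Excess (points) |
|---|---|---|---|
| 0 | 50.0% | 50.0% | 0 |
| 0.2 | 58.7% | 56.4% | 2.3 |
| 0.3 | 63.2% | 59.7% | 3.5 |
| 0.4 | 67.8% | 63.1% | 4.7 |
| 0.5 | 72.5% | 66.7% | 5.8 |
| 0.6 | 77.5% | 70.5% | 7.0 |
| 0.7 | 82.8% | 74.7% | 8.2 |

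**Step 4: does it matter whose data set the cut-points?** Simulation of 40 drivers × 12 drives, 200 runs per setting, with assumed within-driver correlations of SDLP of 0.3, 0.5 and 0.7 and r of 0.3 and 0.5. Taking the cut-points from the 39 training drivers instead of all 40 changed the label of about 1% of drives (0.9% to 1.2%) and moved accuracy by less than 0.1 point. For example, with within-driver correlation 0.5 and r = 0.5, accuracy was 72.44% with pooled cut-points and 72.36% with training-only cut-points.

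**The case against.** The strongest reply is that the exclusion is deduced, not written. The text would allow a model trained on outer thirds and tested on every drive. The plan to report macro- and weighted averages in case of class imbalance shows that the authors do not treat balance as guaranteed, and a condensed article may leave the handling of middle values to the full protocol. Part of this stands: the exclusion must be described as inferred. It does not remove the point. The article itself fixes two cut-points, two classes and near-equal sizes, and any other reading contradicts its own balance statement. The averaging of metrics is a precaution that says nothing about where middle values go.

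A second reply is that the study is preliminary and exploratory, with the OSS as primary outcome and resting-state EEG as secondary. That is a fair reason for moderate severity. Prediction is still the second main objective, and the Discussion states a forecasting use.

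A reader might also infer that cut-points from the whole SDLP distribution break the article's leakage rule. The documents do not support this. The rule names preprocessing, feature selection and hyperparameter tuning. Outcome labelling is not listed, and thresholds checked by experts can be read as a fixed outcome definition. Step 4 shows that the effect is negligible in any case.

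**Conclusion.** The concern holds in a limited form. As written, the outcome definition is coherent only if the middle third is left out, and nothing spares the held-out participant from that exclusion. Performance figures obtained that way describe extreme groups and overstate what an unselected driver would see. For assumed correlations of 0.3 to 0.6, accuracy is about 3.5 to 7 points too high relative to all drives with a median split. This size rests on bivariate normality, on the assumed correlation and on the median split as comparator.

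A reader might infer that any above-chance finding is therefore spurious. That does not follow: with no signal the excess is zero, so the planned permutation test against chance is not invalidated. What suffers is the size of the reported performance, not the test of whether there is any.

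The labelled unit is unclear, since the text speaks of categorizing participants although each participant drives repeatedly. The direction of the bias is the same for either unit. Severity: moderate.

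**What to change.** In Predictive Models Using Resting State EEG:
- State how SDLP values between the two percentiles are handled, and whether the labelled unit is the drive or the participant.
- Report test performance on every drive of the held-out participant, using one cut-off (for example the training-fold median) or continuous SDLP. Training may still use the outer thirds.
- Keep the outer-thirds result as a labelled secondary analysis.
- Compute the cut-off within the training participants of each fold. This is a minor consistency repair and will hardly change the result.

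The cost is a change of wording and a re-run on data already collected; the article says the analysis is still under way. The downside is a lower headline accuracy.

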**Methods:**

Designed as a single-center, nonrandomized, single-group study, this investigation will evaluate drowsiness and cognitive performance in 40 healthy volunteers exposed to 2 sleep deprivation conditions simulating real-world occupational scenarios. The primary outcome will be the Objective Sleepiness Scale (OSS) and its automated analysis, with a focus on its ability to measure objective wakefulness as assessed by the maintenance of wakefulness test (MWT). Secondary outcomes will include multimodal resting-state EEG markers, subjective and objective sleepiness measures, performance on a simulated driving task, attention, executive function, and vigilance assessments, as well as sleep quality, sleep quantity, and mind-wandering. The influence of sociodemographic and clinical variables on the measurement and prediction of drowsiness will also be systematically examined.

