### Experimental Session 1: Fragmented Sleep

This session lasted for 3 consecutive nights and days, during which sleep was recorded. In order to induce sleep pressure on day 3, the third night was fragmented (with 2 imposed wake-ups, during which attentional and vigilance tests were carried out). Three blocks of behavioral tests were conducted during the third day (Figure 1A). One block of tests is 4 hours long and includes, in a fixed order, a driving simulation, cognitive tests, evaluation of sleep pressure, and self-assessments of drowsiness and mind-wandering, while continuous EEG is recorded (Figure 2).

The detailed schedule of days and nights is organized as follows:

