### Data Analysis

#### Statistical Analysis

The analyses will be performed using R version 4.4.2 (R Foundation for Statistical Computing) and IBM SPSS Statistics version 27 (IBM Corp) software for Windows. The normality of the data will be assessed using the Shapiro-Wilk normality test, the equality of variance will be evaluated with the Levene test, and the sphericity of the data will be checked using the Mauchly test. Continuous variables will be expressed as means and categorical variables as proportions (%). *P* values less than .05 will be considered statistically significant.

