### Benefits of 24-Hour EEG

As part of our study protocol, we perform continuous EEG-based monitoring of drowsiness during a 24-hour sleep deprivation period and throughout a subsequent night following daytime recovery sleep. This presents a compelling opportunity to deepen our understanding of the temporal dynamics of sleep pressure and vigilance regulation. Such long-term recordings can capture natural fluctuations in alertness due to circadian and homeostatic processes, as well as individual susceptibility to sleep loss. This comprehensive dataset could inform the development of more robust and generalizable algorithms capable of detecting drowsiness across a wide range of real-world scenarios and time frames.

Moreover, a 24-hour EEG assessment allows the identification of individual variability in drowsiness expression and recovery, potentially enabling personalized predictive models. Such models could dynamically adapt to a user’s physiological state, thereby enhancing the precision and timeliness of drowsiness detection. This approach aligns with the growing emphasis on personalized medicine and human-centered design in neurotechnology.

Developing algorithms trained on 24-hour EEG data may also support the integration of drowsiness monitoring into wearable or minimally invasive systems. By learning to identify EEG markers that remain consistent across different levels of activity, posture, and time of day, these algorithms could eventually be embedded in real-time applications, providing continuous monitoring and early warnings to mitigate fatigue-related risks.

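### The resting-state classifier is evaluated by leave-one-subject-out with no result named by session or time of day, so an above-chance pooled result could arise with no skill in the fragmented-sleep session, or from a model that only tracks day versus night or hours awake

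*Protocol article*

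**What the plan says.** The abstract describes volunteers "exposed to 2 sleep deprivation conditions simulating real-world occupational scenarios". The Introduction gives the resting-state EEG the aim of predicting drowsiness and its functional consequences whatever the preceding time awake. Its closing hypothesis, which covers both the OSS and the resting-state EEG, adds that this should hold at any hour. Principal Findings in the Discussion repeats the aim about time awake.

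The evaluation is set out in Predictive Models Using Resting State EEG:

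- Hold-out unit: "A leave-one-subject-out cross-validation strategy will be applied to provide a robust evaluation under intersubject variability". The inner set for tuning and feature selection is also drawn by participant.
- Outcome: two classes of SDLP, defined from the 33rd and 66th percentiles of a single SDLP distribution.
- Metrics: accuracy, precision, recall and F1, "reporting both macroaveraged and weighted-averaged metrics to account for potential class imbalance".
- Chance: "Bootstrapping and permutation testing will be applied to evaluate the statistical significance and robustness of the results". Under Statistical Analysis, *P* "values less than .05 will be considered statistically significant".

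The schedule is uneven. For session 1, "Three blocks of behavioral tests were conducted during the third day", running from 8 AM to 8 PM. Session 2 has six blocks over 24 hours from 8 AM, then three more from 8 PM to 8 AM the following night. Each block contains one driving simulation.

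**The concern.** The named metrics are averaged over classes, and none is tied to a session or a time segment. Leave-one-subject-out answers whether a model carries over to a new person on the same schedule. Whether it works in each part of that schedule is a separate question, and the study's own aim depends on it.

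Two failures could sit inside a good pooled figure. First, the model could have no skill in the on-call session, which supplies a minority of the drives. Second, the model could separate night from day, or long from short wakefulness, and score well because SDLP is worse at night, without telling a good drive from a poor one at a given time. The second failure would contradict the aim of prediction independent of time awake. It is also easier to reach because sleep history is among the optional covariates.

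**Working it through.** The article states no accuracy, power or sample-size figure to reproduce; Sample Size Calculation says that 40 was set arbitrarily. All accuracies, intraclass correlations (ICCs) and design effects below are assumptions, shown over a range.

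**1. Drives per segment** (from the two session descriptions, one drive per block, 40 participants)

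| Segment | Blocks | Drives |
|---|---|---|
| Session 1, 8 AM–8 PM | 3 | 120 |
| Session 2 day, 8 AM–8 PM | 3 | 120 |
| Session 2 night 3, 8 PM–8 AM | 3 | 120 |
| Session 2 night 4, 8 PM–8 AM | 3 | 120 |
| Total | 12 | 480 |

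Session 1 share = 120/480 = 25%. If the middle third of SDLP is dropped (a reading; the article does not say so), about 480 × 2/3 = 320 drives are labelled. That is 80 per segment if the loss is proportional.

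**2. No skill in session 1**

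Pooled accuracy = s × a1 + (1 − s) × a2, where s is the session 1 share, a1 the accuracy in session 1 and a2 that in session 2. Taking a1 = 0.50 as no skill assumes balanced classes within session 1.

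- a2 = 0.75: 0.25 × 0.50 + 0.75 × 0.75 = 0.6875.
- a2 = 0.60, 0.70, 0.80, 0.90: 0.575, 0.65, 0.725, 0.80.
- If the labelled share of session 1 is 15% or 35% instead, a2 = 0.80 gives 0.755 or 0.695.

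**3. Would the pooled test detect it?**

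With 320 drives and a design effect of 2, the standard error under chance is √(0.25 × 2/320) = 0.0395. For 0.6875, z = 0.1875/0.0395 = 4.74.

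The smallest session 2 accuracy that reaches one-sided 0.05 is (c − 0.125)/0.75, where c = 0.5 + 1.645 × √(0.25/n_eff) and n_eff = 320/(1 + 7 × ICC). It is 0.56 at ICC 0, 0.61 at ICC 0.3 and 0.63 at ICC 0.5.

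A simulation used 40 participants with 2 session 1 and 6 session 2 labelled drives each, and a one-sided 0.05 test on participant accuracies in place of the permutation test. With chance performance in session 1, the pooled test was significant in 57–84% of runs at a2 = 0.60, 86–99% at 0.65 and 98–100% at 0.70 (ICC 0.3 down to 0). A test on session 1 alone was significant in about 5%, the nominal level.

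**4. A model that only tracks day versus night**

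By step 1, 6 of 12 drives fall between 8 PM and 8 AM. Take a rule that calls every night drive Poor and every day drive Good. Suppose a fraction q of labelled day drives are Good and q of labelled night drives are Poor, with half the labelled drives in each. Pooled accuracy = 0.5q + 0.5q = q. For q = 0.60, 0.65, 0.70, z = 0.10/0.0395 = 2.53, 0.15/0.0395 = 3.79 and 0.20/0.0395 = 5.06.

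Within each segment the rule predicts one class only. Recall is 100% for that class and 0% for the other, so balanced accuracy is 50%. Permuting labels within the segment leaves its number of correct predictions unchanged, so it cannot look significant there. Raw accuracy by segment would still show q, which is why balanced accuracy is needed.

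**5. Is a session 1 result informative?**

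In the same simulation, a test on about 80 session 1 drives had about 82% power for a true accuracy of 0.65 and 96.5% for 0.70 (ICC 0.1).

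**The case against.** The strongest reply is that the article is silent here rather than wrong. It does not say that one pooled figure will be the only result, and a statistical analysis plan that is not shown may break results down by session. That stands: nothing here shows that such results are excluded. The point is more than missing detail because the article fixes the evaluation down to the inner validation set, class averaging and chance testing, and what it fixes cannot test the independence from time awake that it sets as an aim.

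A reader might infer that a model useless in the on-call session would be reported as validated for it. The documents do not support that. No accuracy threshold for validation is set, the study is called preliminary and exploratory, and session 2 accuracy is unknown. The supportable word is could.

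A reader might also blame the lack of a scenario hold-out, or read "robust and generalizable algorithms capable of detecting drowsiness across a wide range of real-world scenarios and time frames" as a claim of transfer to new scenarios. Neither holds. Each held-out participant contributes drives from both sessions, so the planned predictions already contain what is needed to expose a session 1 failure; they only have to be tabulated. The quoted phrase belongs to a conditional Discussion remark about what the 24-hour data might inform.

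Finally, the sizes are constructed. Session 1 has no night drives, so its labelled drives may lean towards Good; then 50% is not the no-skill level there and the labelled share need not be 25%. This limits the exact figures and is a reason for balanced accuracy.

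**Conclusion.** The point holds in limited form. The evaluation as described can show prediction in a new person on this schedule. A pooled above-chance result would not by itself show skill in the fragmented-sleep session, or skill beyond tracking day versus night or hours awake. Under the assumptions above, a pooled accuracy of 57.5% to 80% is compatible with chance performance in session 1, and a pure day–night rule reaches whatever day–night imbalance the labels have.

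The 3-in-12 count and the clock times come from the article. The accuracies, the ICCs, the design effect, the dropping of the middle third, its proportional spread and class balance within session 1 are assumed. Nothing in the article suggests that session 1 skill will in fact be absent. The change should be made, because it lets the study test its own hypothesis at little cost.

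**What to change.** Keep leave-one-subject-out. Before the ongoing analysis reaches these results, prespecify:

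1. Held-out metrics reported separately for session 1, session 2 day (8 AM–8 PM), night 3 and night 4, beside the pooled figure.
2. Balanced accuracy in each segment, with the class counts, because class balance may differ between segments.
3. Chance tests by permuting labels within each segment.
4. Any validity statement limited to the segments where performance exceeds chance.

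Training on one session and testing on the other may be added as a supplementary analysis only. It asks about transfer to an unseen schedule, and it is confounded by the fixed session order and by time of day, since session 1 has no night drives.

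The cost is computation and wording; no new data are needed. The price is precision: with about 80 labelled drives instead of 320, the standard error is √(320/80) = 2 times the pooled one at equal design effect, and a segment with skewed classes will be less precise still. Time awake also rises across the three blocks of a segment, so the split reduces the hours-awake explanation without removing it. The report should say so.

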Nevertheless, current real-time spontaneous drowsiness detection systems continue to face several challenges. First, they typically require continuous wear by the operator, which complicates their implementation in real operational settings. Second, the detection of drowsiness often occurs too late to prevent its functional consequences. Therefore, the development of EEG-based tools allowing the prediction of drowsiness and its behavioral consequences—rather than detecting its presence—would mark a significant advancement in ensuring operator safety. In experimental protocols, routine EEG bio-calibrations, performed with eyes open and eyes closed, are critical for assessing signal quality and characterizing an individual’s resting-state brain activity. Resting-state EEG recordings, under both eyes-opened and eyes-closed conditions, have been used to evaluate task performance and drowsiness levels [28-31]. An algorithm developed by the University of Leipzig (VIGALL, The Vigilance Algorithm Leipzig) can identify 7 states of somnolence during a 5-minute resting-state EEG but requires the recording of at least 19 EEG leads (25 recommended), making it unusable in real operating conditions [32]. However, these short measures offer a promising avenue for prediction. Indeed, a brief, iterative, and easy-to-administer resting-state assessment could enable early identification of drowsiness and its potential cognitive and behavioral impacts, thereby facilitating timely and effective preventive interventions.

The objective of this study is to validate—under sleep deprivation conditions reflecting real-life occupational scenarios (such as delayed, fragmented, or disturbed sleep, typically experienced during night work, shift work, or on-call duty)—the ability of the OSS and its automatic analysis by the MEEGAWAKE algorithm to accurately assess drowsiness and its associated cognitive and behavioral consequences. In addition, the study aims to evaluate whether automatic analysis of resting-state EEG can reliably predict drowsiness and its functional outcomes, independently of the duration of prior wakefulness. Such predictive capability could enhance risk assessment and contribute to the prevention of sleepiness-related accidents in operational settings.

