We hypothesize that both the OSS and resting-state EEG, potentially adjusted for interindividual variability in sleepiness susceptibility, can effectively measure and/or predict drowsiness and its behavioral consequences, including the inability to maintain wakefulness and impairments in sustained attention and vigilance, regardless of the time of day. This approach may provide a robust framework for identifying and mitigating risks associated with drowsiness in safety-critical environments.

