## Discussion

### Principal Findings

The objective of this study is to validate a new, easily implementable spontaneous drowsiness measurement, derived from OSS criteria and based on the automatic analysis of a limited number of EEG channels, able to reflect manifest drowsiness, particularly the ability to stay awake and the associated cognitive and behavioral consequences, regardless of the time of day. In addition, the study aims to evaluate whether iterative resting-state EEG can reliably predict drowsiness and its functional outcomes, independently of the prior duration of wakefulness. These measurements will enable the early assessment of drowsiness, allowing for the prediction of the ability to maintain wakefulness and/or of both simple and/or complex cognitive impairments associated with drowsiness.

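### The resting-EEG model is claimed to predict independently of time awake and clock time, but is tested only against chance and other algorithms, so EEG could pass as a proxy for the schedule

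*Protocol article*

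**What the plan says.** The Introduction states the aim of evaluating whether automatic analysis of resting-state EEG "can reliably predict drowsiness and its functional outcomes, independently of the duration of prior wakefulness". Principal Findings in the Discussion repeats it almost word for word: "can reliably predict drowsiness and its functional outcomes, independently of the prior duration of wakefulness". The hypothesis in the Introduction extends the claim to "impairments in sustained attention and vigilance, regardless of the time of day".

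Predictive Models Using Resting State EEG fixes the analysis. The end point is the standard deviation of lateral position (SDLP) in simulated driving, split into good and poor performance "based on the 33rd and 66th percentiles of the SDLP distribution". CatBoost is fitted on EEG recorded before the task, evaluated by leave-one-subject-out cross-validation, and set beside four other classifiers. On other inputs the section says "Demographic and behavioral covariates (eg, age, gender, chronotype, daydreaming frequency, and sleep history) will be optionally included to account for residual interindividual variability". On inference it says "Bootstrapping and permutation testing will be applied to evaluate the statistical significance and robustness of the results", the purpose being to exclude chance as the explanation.

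The section names no reference model without EEG, no comparison of performance with and without EEG, and no evaluation within block or adjusted for hours awake or clock time.

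**The concern.** The Experimental Timeline and the two session schedules give every participant the same sessions in the same order, with 3 + 6 + 3 = 12 test blocks at the same clock hours. Both sessions are built to raise sleep pressure, so resting EEG and SDLP can both be expected to shift with the schedule. Leaving one participant out does not remove this, because the held-out person followed the same schedule as the training set.

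A classifier can therefore beat chance because EEG reflects how long everyone has been awake and what time it is, and for no other reason. That result would be compatible with the independence claim and equally compatible with its opposite. At stake is the interpretation of the second of the two main objectives. If block number alone predicts poor driving at least as well as EEG does, the study has not shown what EEG adds in an operational setting where hours on duty are already known.

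**Working it through.** **No figure to reproduce.** The article gives no target accuracy, effect size or power. Under Sample Size Calculation, "this number has been arbitrarily set to 40 healthy volunteers". The size of the problem therefore has to be shown over a range of assumptions.

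**Inputs from the article.** 40 participants; 12 blocks each; classes from the outer thirds of SDLP; leave-one-subject-out; significance at .05.

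**Assumptions.** One drive per block; the middle third of SDLP is dropped; SDLP and EEG are linear in hours awake; participants account for 40% of SDLP variance (20–60% in step 2); 7 AM waking on day 2 of session 2; labels are permuted without restriction. The article does not state the permutation scheme.

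**Step 1: the bar set by chance.** 40 × 12 = 480 drives, of which about 2/3 × 480 = 320 fall in the two classes. The exact binomial 5% threshold is 176/320 = 0.55. The normal approximation is 0.5 + 1.645 × √(0.25/320) = 0.546. Both ignore clustering by participant.

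**Step 2: the bar set by the schedule.** A rule that knows only the block predicts the training-set majority class for that block.

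| Share of SDLP variance due to time awake | Mean accuracy | Passes permutation test |
|---|---|---|
| 0% | below 0.50 | 0–1.5% |
| 5% | 0.56–0.58 | 32–42% |
| 10% | 0.62–0.63 | 73–83% |
| 20% | 0.69 | 97–99% |
| 30% | 0.74–0.75 | at least 99% |

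This is not the planned model. It shows the level that EEG would need to exceed.

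**Step 3: EEG as a pure proxy.** SDLP = block + participant + residual. EEG = block + its own independent participant part + its own residual. Given block, EEG carries no information on SDLP. A one-dimensional classifier on EEG is run leave-one-subject-out. Ranges are over repeated runs of this set-up.

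| Block share, SDLP / EEG | EEG accuracy | Passes unrestricted permutation | Block-only accuracy |
|---|---|---|---|
| 5% / 5% | 0.51–0.52 | 19–23% | 0.56–0.58 |
| 10% / 10% | 0.52–0.54 | 28–36% | 0.62–0.64 |
| 20% / 10% | 0.56 | 50–58% | 0.69–0.71 |
| 20% / 20% | 0.59 | 74–80% | 0.69–0.71 |
| 40% / 40% | 0.68–0.69 | over 99% | 0.79–0.82 |

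Block-only accuracy was higher than EEG accuracy in every setting.

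The low rows need care. With no block effect at all, and participants accounting for 40% of the variance of both variables, the unrestricted test still passed in about 15% of 400 runs, because it ignores clustering by participant. At a 5% share most of the excess over 5% therefore comes from clustering. From about 20% upward the schedule dominates.

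**Step 4: a null that keeps the schedule.** When whole EEG records were swapped between participants with block positions kept, rejection was 2–6%, close to nominal. One smaller set, with 100 runs per setting, ranged from 3% to 11%.

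**Step 5: can the design separate the two?** Partly. In session 2 the 8 PM, midnight and 4 AM blocks occur on two nights. On night 3, with 7 AM waking, hours awake are 20 − 7 = 13, 24 − 7 = 17 and 28 − 7 = 21. On night 4, after recovery sleep ending at 1 PM, they are 20 − 13 = 7, 24 − 13 = 11 and 28 − 13 = 15. The 8 AM, noon and 4 PM blocks also occur after a fragmented night (session 1) and after a laboratory night without imposed wake-ups (session 2).

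**The case against.** The strongest reply is that tracking sleep pressure is the intended mechanism. The Discussion describes resting EEG as a way to quantify it, and the second objective under Methods speaks only of impairments linked to drowsiness. Independence from prior wakefulness could then mean that the tool works at any wake duration without being told what it is. That reading is possible. Even so, the article would need to show performance within levels of wake duration or hour, and pooled better-than-chance accuracy does not show that either.

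Several stronger readings are tempting and are not supported:

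- *A model that merely reads the schedule would pass.* Block, clock time and hours awake are not listed inputs. The risk is that EEG acts as a proxy for them.
- *A proxy is bound to pass.* At 5–10% shares it usually fails.
- *The permutation test is unrestricted.* The scheme is not stated. A restricted one may be intended, and an article may leave that to the full plan.
- *Clock time and time awake are wholly confounded.* Session 2 partly separates them.
- *Accumulated sleep deprivation is a fixed input.* The Discussion mentions integrating characteristics "such as age, sex, chronotype, and accumulated sleep deprivation", but the analysis section makes covariates optional. If included, sleep history is a further input. It is not a comparator.

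The study also calls itself preliminary and exploratory, and its primary outcome is the Objective Sleepiness Scale. That tempers the consequences, but the article still speaks of validating the models. Nor is this only brevity: the article itself sets out the comparators and the better-than-chance criterion, and these do not answer its stated aim.

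**Conclusion.** The concern holds as a mismatch between claim and test. Better-than-chance accuracy, or one algorithm outperforming another, cannot establish independence from hours awake or clock time when no comparison contains them and all participants share one schedule. This part rests on the article's text alone.

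The size is conditional. With no EEG–SDLP link beyond block, a proxy passes an unrestricted test in roughly 20–35% of runs at 5–10% variance shares (partly through clustering), about three quarters at 20%, and nearly all at 40%. These figures depend on assumed variance shares, a linear time-awake effect, one drive per block and an unrestricted permutation, none of which the article states. They show that the risk can be substantial. They do not show that it will materialise.

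**What to change.** 1. In the same leave-one-subject-out folds, fit a benchmark without EEG, using hours awake, clock time, session and block, and the listed covariates including sleep history.
2. Fit the same model plus resting EEG. Report the gain in held-out performance over the benchmark, with an interval from bootstrapping participants.
3. Test the gain by permuting EEG records across participants within block position, so that the null keeps the schedule. Use the session 2 clock hours that recur at different hours awake to help separate the two influences.
4. Base any conclusion of independence from prior wakefulness on this gain. Otherwise limit the wording in the Introduction and Principal Findings to better-than-chance prediction.
5. Analysis began in June 2025 after database lock, so ordinary pre-specification is no longer available. Record the change in a dated addendum before the model results are examined, and state what had already been seen.

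The cost is one extra model in the existing pipeline and a restricted permutation, with no new data. The downside is that the claimed gain will be smaller than the raw accuracy.
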